# Effect of stellate ganglion block on the prevention of posttraumatic stress disorder in patients undergoing emergency ocular trauma surgery: protocol for a randomized, double-blind, placebo-controlled trial

**DOI:** 10.3389/fmed.2025.1663506

**Published:** 2025-10-02

**Keywords:** stellate ganglion block, posttraumatic stress disorder, emergency, ocular trauma, protocol

## Abstract

**Background:**

Post-traumatic stress disorder (PTSD) is a prevalent and debilitating mental health condition that often develops after exposure to traumatic events. Stellate ganglion block (SGB) has been shown to alleviate PTSD symptoms, suggesting its potential as a preventive intervention, particularly in patients undergoing emergency ocular trauma surgery. However, the efficacy of SGB in preventing the onset of PTSD has not been clearly established.

**Methods:**

This dual-center, randomized, double-blind, placebo-controlled trial will enroll 300 adult patients undergoing emergency ocular trauma surgery. Participants will be randomly assigned, in a 1:1 ratio and stratified by age (<65 or ≥65 years), to either the SGB group or the placebo group (*n* = 150 per group). Each participant will receive either an active right stellate ganglion block or a sham procedure administered 15 min prior to the induction of anesthesia. The primary outcome is the difference in the incidence of PTSD at 1 month after surgery. Secondary outcomes include the severity of PTSD, delayed-onset PTSD, the four core symptom clusters (intrusive re-experiencing, avoidance, negative alterations in cognition or mood, and hyperarousal and reactivity), the severity of dissociative symptoms, Beck Anxiety Inventory (BAI) scores at 24, 48, and 72 h postoperatively; Visual Analog Scale (VAS) sleep scores at 24, 48, and 72 h postoperatively; Numerical Rating Scale (NRS) pain scores at 24, 48, and 72 h postoperatively; Heart Rate Variability (HRV) measured intraoperatively and at 24 and 48 h postoperatively; recovery time; extubation time; Richmond Agitation-Sedation Scale (RASS) scores; and length of hospital stay. Safety outcomes will include neck pain, dizziness, tinnitus, respiratory depression, anaphylaxis, sinus bradycardia (defined as heart rate <50 beats/min), hematoma formation, infection, severe arrhythmia, pneumothorax, and complications related to general or spinal anesthesia. All data will be analyzed using a modified intention-to-treat (mITT) approach.

**Discussion:**

This study aims to evaluate the efficacy and safety of SGB for the prevention of PTSD in patients undergoing emergency ocular trauma surgery.

**Clinical trial registration:**

ChiCTR2500102717, www.chictr.org.cn/showproj.html?proj=270046.

## Introduction

Post-traumatic stress disorder (PTSD) is a mental health condition that develops in individuals following exposure to threatening, severe, or catastrophic events. Clinically, it is characterized by symptoms such as hypervigilance, delayed reactions, and intentional avoidance of trauma-related stimuli (1, 2). Epidemiological studies report a lifetime prevalence of PTSD ranging from 13.0 to 20.4% in women and from 6.2 to 8.2% in men (3). The incidence of PTSD following trauma-related hospitalization has been reported to be as high as 23% (4). Once diagnosed, PTSD not only affects a patient’s psychological well-being but also has detrimental effects on physical health, social relationships, and occupational functioning. It significantly impairs quality of life and increases the risk of comorbid mental disorders such as depression and suicide (5, 6).

Ocular trauma refers to mechanical, physical, or chemical injuries to the eye and its associated structures, resulting in structural and/or functional impairment (7). In China, the incidence of ocular trauma is relatively high, with an estimated 5 to 12 million new cases reported annually (8). Patients with ocular trauma often experience varying degrees of visual impairment, and visual deprivation may disrupt spatial orientation and intensify feelings of fear (9). Additionally, trauma-induced pain can reinforce traumatic memories through mechanisms of central sensitization, while visible facial injuries may contribute to emotional distress, increasing the risk of anxiety, depression, and PTSD in these patients (10, 11). Studies have shown that up to 33% of individuals with ocular trauma may develop PTSD (9, 11). Therefore, early and timely intervention is crucial for reducing the risk of PTSD in this population.

Stellate ganglion block (SGB) involves the injection of a local anesthetic into the stellate ganglion at the base of the neck to temporarily block sympathetic nerve activity (12). It is thought to exert its therapeutic effects by modulating the sympathetic nervous system through cervical sympathetic blockade (13). While most previous studies (14–18) have investigated SGB as a treatment for established PTSD, the disorder is often chronic and difficult to manage once it develops, even with available therapies (3, 14). Preventive intervention may therefore offer greater benefit, particularly in high-risk populations such as patients with ocular trauma. The acute perioperative period represents a critical window for fear memory consolidation, and timely modulation of sympathetic activity may disrupt this process and reduce the likelihood of PTSD onset. Moreover, ultrasound-guided SGB is a rapid, safe, minimally invasive, and cost-effective procedure (19), supporting its potential as a practical preventive strategy in this setting. Our group has accumulated relevant experience in this field. We previously investigated preventive strategies for PTSD in patients undergoing emergency trauma surgery (20–22), which provided valuable insights into study design and the perioperative application of SGB. In addition, our preclinical work demonstrated that SGB could attenuate the consolidation of conditioned fear memory by modulating the locus coeruleus–basolateral amygdala circuit, thereby offering mechanistic support for its use in early trauma settings (20). Collectively, these prior studies provide both methodological and biological foundations for the present trial, reinforcing its reliability and feasibility.

This study aims to assess the efficacy and safety of preoperative SGB in reducing the incidence of PTSD in patients undergoing emergency ocular trauma surgery.

## Methods

This protocol follows to the Standard Protocol Items: Recommendations for Interventional Trials (SPIRIT) guidelines, which is detailed in Supplementary file 1.

### Study design and patients

This is a dual-center, prospective, randomized, patient- and assessor-blinded, parallel-group, controlled clinical trial. A total of 300 patients will be recruited from the First Central Hospital of Baoding and the 82nd Group Army Hospital of the People’s Liberation Army (PLA). Recruitment is scheduled to take place from May 22, 2025, to November 22, 2025. Follow-up period is from November 23, 2025, to May 22, 2026. A detailed study flow diagram is shown in Figure 1.

**Figure 1 fig1:**
[figure not shown]
Study flow diagram. SGB, stellate ganglion block.

### Inclusion criteria

Patients who meet the following criteria will be included:Age 18 or older.Acute unilateral or bilateral ocular trauma and scheduled for surgery under general anesthesia.American Society of Anesthesiologists (ASA) physical status I-III E.Provided informed consent, with approval from both patients and their families.

### Exclusion criteria

The exclusion criteria include:A known allergy to ropivacaine.Infection of the skin on the neck.Combine severe neurological or mental disorders unable to undergo assessmtent.Craniocerebral or spinal cord injury.Shock decompensation.Associated with multiple and complex injuries and requiring concurrent implementation of multiple surgical procedures.Severe atrioventricular block or bradyarrhythmia with a baseline heart rate lower than 50 beats/min.Severe visual, hearing, or speech impairments that prevent the completion of assessment.

### Primary outcome

The primary outcome is the difference in the incidence of PTSD between the two groups at 1 month postoperatively, assessed using the Clinician-Administered PTSD Scale for DSM-5 (CAPS-5). The CAPS-5 is a structured diagnostic interview widely regarded as the gold standard for PTSD assessment. Neuropsychological evaluations will be conducted by professionally trained anesthesiologists who are blinded to group allocation and will perform assessments in a calm and controlled environment. Data analysts will also remain blinded to treatment assignments. The CAPS-5 provides both a diagnostic determination (presence or absence of PTSD) and a continuous measure of PTSD severity, including the four core symptom clusters: intrusions, avoidance, negative alterations in cognition and mood, and arousal/reactivity. The assessment can be administered by appropriately trained clinicians or paraprofessionals.

### Secondary outcomes

Secondary outcomes include the severity of PTSD, delayed-onset PTSD, the four core symptom clusters (intrusive re-experiencing, avoidance, negative alterations in cognition or mood, and hyperarousal/reactivity), and the severity of dissociative symptoms. Other secondary outcomes include Beck Anxiety Inventory (BAI) scores (range 0–84, higher scores indicating greater anxiety) assessed at 24, 48, and 72 h postoperatively; Visual Analog Scale (VAS) sleep scores (range 0–10, with 0 representing best and 10 worst sleep quality) at the same time points; and Numerical Rating Scale (NRS) pain scores (range 0–10, higher scores indicating more severe pain) also at 24, 48, and 72 h. Heart Rate Variability (HRV) will be assessed intraoperatively and again at 24 and 48 h postoperatively. Recovery time is defined as the interval from cessation of general anesthesia maintenance medication to recovery of consciousness, while extubation time is defined as the interval from cessation of anesthesia maintenance medication to extubation. The Richmond Agitation-Sedation Scale (RASS) will be used to evaluate patients’ level of consciousness, sedation, agitation, and their severity. Finally, the length of hospital stay will also be recorded as a secondary outcome.

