### Study interventions

Patients will receive either a right SGB or a sham procedure 15 min prior to induction of anesthesia. In the SGB group, 5 mL of 0.5% ropivacaine will be injected around and into the stellate ganglion at the level of the C6 anterior tubercle under ultrasound guidance (23). In the control group, 2 mL of preservative-free normal saline will be injected into the deep musculature anterolateral to the anterior tubercle of C6, deliberately avoiding the stellate ganglion. The injection of 2 mL saline into a region other than the stellate ganglion is mainly for evaluating the placebo effects of the study procedures. Apart from the injectate and its site of deposition, all other procedures, including patient preparation, positioning, ultrasound guidance, and needle insertion technique, will be identical in both groups.

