### Data collection and monitoring

Patient data will be thoroughly reviewed by the research team using individual electronic medical records. The collected baseline variables will include age (years), sex, body mass index (BMI, kg/m^2^), education level, preoperative medications, comorbidities, American Society of Anesthesiologists (ASA) physical status classification, smoking status, and the time from injury to anesthesia induction, among others. Post-discharge information will be obtained via direct interviews or telephone follow-ups and recorded in the follow-up management system. In addition, major life events such as serious illnesses, accidents, or the death of close family members will also be documented.

All data will be recorded on case report forms (CRFs) and entered into a secure electronic database under the supervision of the principal investigator. An independent Data Monitoring Committee (DMC) will oversee the data collection process throughout the study. Upon completion of data entry, the database will be locked and anonymized datasets will be submitted to an independent statistician for final analysis according to the predefined statistical analysis plan.

Any serious adverse events (SAEs), whether related or unrelated to the study intervention, must be reported immediately to the principal investigator. Appropriate medical measures will be initiated by the perioperative care team to ensure patient safety. In addition, all SAEs will be reported to the DMC within 24 h for evaluation, including assessment of whether protocol modifications or study termination is required.

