### Sample size calculation

According to the literature, the incidence of PTSD at 1 month after trauma surgery is approximately 23.2% (21). Previous epidemiological studies have reported rates up to 30–33% in patients with ocular trauma, substantially higher than in the general trauma population (9, 11). Based on these data and our small pilot observation, we set the expected PTSD incidence in the control group at 26%. We therefore adopted 26% as a conservative estimate to guide the sample size calculation. This conservative approach ensures that statistical power will not be underestimated if the true incidence in our study population is somewhat lower than that reported in epidemiological studies, while still remaining consistent with the published range. We hypothesize that SGB will reduce the risk of postoperative PTSD by 50% in patients undergoing emergency ocular trauma procedures. Using a two-sided test with a significance level of *α* = 0.05 and 80% power, a minimum of 142 participants per group is required. Accounting for an anticipated 10% dropout rate, the final target sample size is 300 patients, with 150 allocated to each group.

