### Statistical analysis

The normality of continuous variables will be evaluated using the Shapiro–Wilk test. Data following a normal distribution will be reported as mean (standard deviation, SD), while non-normally distributed data will be expressed as median (interquartile range, IQR). Group comparisons for normally distributed continuous variables will be conducted using independent t-tests or repeated measures ANOVA, as appropriate. For non-normally distributed variables, analyses will be performed using the Mann–Whitney U test or generalized estimating equations (GEE) to account for repeated measures and potential correlations. Categorical data will be presented as counts (percentages) and analyzed using the chi-square test or Fisher’s exact test, as appropriate, based on expected frequency distributions.

The 1-month postoperative prevalence of PTSD, defined as the primary endpoint, will be compared between groups using the chi-square (*χ*^2^) test. Group differences will be reported as odds ratios (ORs) with 95% confidence intervals (CIs). To control for potential confounders, logistic regression models will be used to obtain adjusted ORs. Subgroup analyses will also be conducted using logistic regression to examine treatment-by-covariate interactions.

Analyses of the primary outcome will primarily follow a modified intention-to-treat (mITT) approach, including all randomized participants with available data, regardless of protocol adherence. A per-protocol (PP) analysis will also be performed, excluding patients with major protocol deviations or who withdrew consent, to assess the treatment effect among fully adherent participants. No multiple testing correction is planned for secondary outcomes; these results will be interpreted as exploratory.

To evaluate CAPS-5 score changes over time (at 1- and 6-month follow-ups), repeated measures analysis will be performed using a covariate-adjusted linear mixed model (LMM). Fixed effects will include group (SGB vs. control), time (1 month vs. 6 months), and the group-by-time interaction. Potential confounding variables—such as sex, age, Injury Severity Score (ISS), laterality of ocular trauma (unilateral or bilateral), time from injury to surgery, and baseline VAS pain scores—will be entered as covariates. If significant time-by-covariate interactions are detected, they will be incorporated into the model. Results will be presented as least squares means (LSMs) with 95% CIs.

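### Anxiety (BAI) has no score before the block and no baseline term in its planned analysis, so this exploratory comparison is unbiased but less precise than it could be

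*Protocol article*

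**What the plan says.** Secondary outcomes (protocol article) lists BAI scores, range 0–84, "assessed at 24, 48, and 72 h postoperatively". The BAI row of Table 1 marks those three columns and leaves the emergency-room and pre-anesthesia columns empty. Study interventions fixes the order of events: "Patients will receive either a right SGB or a sham procedure 15 min prior to induction of anesthesia". All scheduled BAI scores therefore come after the block.

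Data collection and monitoring names the baseline variables. No anxiety score is among them, although the list is open, ending "smoking status, and the time from injury to anesthesia induction, among others".

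Statistical analysis gives a general rule for continuous outcomes: "Group comparisons for normally distributed continuous variables will be conducted using independent t-tests or repeated measures ANOVA, as appropriate". For non-normal data, "analyses will be performed using the Mann–Whitney U test or generalized estimating equations (GEE"). Neither names a baseline term. The one model with named covariates is for CAPS-5, where "repeated measures analysis will be performed using a covariate-adjusted linear mixed model (LMM"); its covariates are sex, age, Injury Severity Score, laterality, time from injury to surgery and baseline VAS pain. On the status of the outcome, the section says: "No multiple testing correction is planned for secondary outcomes; these results will be interpreted as exploratory".

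**The concern.** The Introduction says that pain, facial injury and visual loss raise the risk of anxiety in these patients, so some of the anxiety measured at 24–72 h may already be present on arrival. Without a pre-block score, whatever part of the spread between patients that score would predict stays in the error term. Randomization is stratified by age only, so nothing else in the design reduces this variation.

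The timing matters because no analysis plan can adjust for a score that was never collected. Patients are consented and characterised in the emergency room before the block, so a place for the score exists. At stake is the width of the confidence interval for early anxiety, not the validity of the comparison.

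**Working it through.** **Plan's own figures.** The document gives no SD, effect size or sample size for BAI, so there is no BAI figure to reproduce. The sample size for the primary outcome does reproduce: 26% versus 13%, two-sided α = 0.05, 80% power, unpooled normal formula, gives 141.9, hence the stated 142 per group. It is needed here only for context.

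**Inputs.**
- Per arm: 150 randomized; with the stated 10% dropout, 150 × 0.9 = 135.
- Two-sided α = 0.05 (Sample size calculation and Statistical analysis).
- Assumed, not in the document: correlation r between pre-block and later BAI; a constant effect of 0.3 SD; equal correlation among all four scores (compound symmetry) where the three later scores are averaged.

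**Single time point.** With the baseline as covariate, the residual variance is (1 − r²) of the original. Power ≈ Φ(0.3 / √(2(1 − r²)/135) − 1.96).

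| r | Variance removed | Power |
|---|---|---|
| no covariate | 0% | 69% |
| 0.1 | 1% | 70% |
| 0.2 | 4% | 71% |
| 0.3 | 9% | 73% |
| 0.5 | 25% | 81% |

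Exact t-test values for the rows with no covariate, r = 0.3 and r = 0.5 are 69.0%, 73.1% and 80.9%. With all 150 per arm, the normal-formula values are 73.8%, 77.7% and 85.1%.

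**Mean of the three scores.** This is closer to the repeated-measures options in the plan. In units of the single-score variance, the mean has variance (1 + 2r)/3 unadjusted and (1 + 2r)/3 − r² adjusted.

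| r | Unadjusted | Adjusted | Reduction | Power unadjusted | Power adjusted |
|---|---|---|---|---|---|
| 0.3 | 0.533 | 0.443 | 17% | about 92% | about 96% |
| 0.5 | 0.667 | 0.417 | 37% | about 85% | about 97% |

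**Covariate or change score.** A change score has variance 2(1 − r): 1.4 times that of the raw score at r = 0.3, and 1.0 times at r = 0.5. It is worse than no baseline at all below r = 0.5.

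**What is still achievable.** Recruitment was scheduled from 22 May to 22 November 2025, 184 days. The article appeared on 2 October, day 133: 133/184 = 72%. If accrual was even and only the last 28% had a baseline score, combining the two sets by inverse variance gives relative information 0.28/(1 − r²) + 0.72. At r = 0.5 this is 1.093, so the single-time variance falls by 1 − 1/1.093 = 9%, not 25%, and power is 73%, not 81%. At r = 0.3 it is 1.028, a 3% reduction.

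**The case against.** The strongest reply is that nothing here is an error. A randomized comparison of post-treatment scores is valid without a baseline, and the outcome is declared exploratory. That stands, and it fixes the weight of the point: an efficiency suggestion.

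Second, a baseline BAI may exist unlisted. The baseline list is open, Table 1 has an unitemised row for baseline characteristics, and baseline VAS pain is used as a covariate without its own row in Table 1. This cannot be excluded. However, the BAI times are stated in the text and in Table 1, they agree, and neither includes a pre-block score. As written, none is planned.

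Third, the gain depends on assumed values. This also stands: at r = 0.1–0.2 it is negligible, and a repeated-measures comparison would already have about 85–92% power for the assumed effect at r = 0.3–0.5. The 69% figure applies to a single time point and should not be read as the power of the whole BAI comparison.

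A reader might infer more than the document supports:
- That chance imbalance in distress cannot be told apart from a block effect. The planned tests and intervals already allow for chance imbalance; adjustment narrows the interval.
- That one score would remove all differences between patients. It removes only the r² share.
- That differences in anxiety before the block are known to be large. No BAI spread is given; the Introduction speaks of raised risk, not of variance between patients.
- That BAI is the secondary outcome nearest the mechanism. The Discussion describes sympathetic activity and names heart rate variability as the objective physiological measure.

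**Conclusion.** The point holds as a minor loss of precision. At one time point the planned BAI comparison carries r² more of the variance than it need: 9% at r = 0.3 and 25% at r = 0.5. The power gain for an assumed 0.3 SD effect is 4 to 12 percentage points at one time (69% to 73% or 81%), and about 4 to 12 points for the mean of three scores (92% to 96%, or 85% to 97%). These figures rest on the assumed r, the assumed constant effect, compound symmetry for the averaged score, and a baseline score in every patient. The last condition can no longer be met for those already enrolled. There is no bias, and the primary PTSD analysis is not touched.

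**What to change.** Add a mark for BAI in the emergency-room column of Table 1, taken before the block and read aloud where vision requires it. State that it enters the 24, 48 and 72 h comparison as a covariate (ANCOVA or a mixed model), not as a change score. If a baseline BAI is already being collected, add it to Table 1 and to the analysis text.

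For patients already recruited, adjust the BAI comparison for the baseline covariates already listed for the CAPS-5 model, and report the missing pre-block score as a limitation.

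The cost is a few minutes at enrolment with an instrument already in use, and an amendment line. Some emergency patients will miss the score, and the benefit falls with the share already enrolled.
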